### Neurocognition assessments

Neurocognition was assessed using a multimethod evaluation administered solely at baseline to identify individual differences in executive functioning (EF) that may predict treatment response. Trait-level attentional control, comprising focusing and shifting dimensions, is assessed with the Attentional Control Scale (ACS) [84], a self-report measure. Inhibitory control is measured with the computerized Go/No-Go (GNG) [85, 86], whereas set-shifting is assessed via the computerized Wisconsin Card Sorting Test (WCST) [87]. Working memory (WM) is assessed via the 2-Back Task (2BT) [88], which instructs participants to track and respond to repeated numbers across successive trials. The GNG, WCST, and 2BT tests are all implemented on the PsyToolKit platform [85, 86]. These performance-based neurocognitive assessments generate accurate scores, error counts, response times (RTs), and signal detection metrics (e.g., d-prime) rather than total scores. Collectively, these measures provide a comprehensive picture of neurocognitive functioning before randomization, enabling the testing of neurocognitive moderators and predictors of treatment (Table 1 and Appendix B).

### Sleep assessments

Sleep functioning and quality are assessed using four self-report assessments administered at baseline, mid-treatment, post-treatment, as well as at 3-, 6-, and 12-month follow-ups to evaluate both proximal and distal changes in sleep patterns. The Sleep Condition Indicator (SCI) [89] assesses insomnia symptoms in ways consistent with DSM-5 diagnostic criteria [66]. The Pre-Sleep Arousal Scale (PSAS) [90] assesses cognitive and somatic arousal during the pre-sleep period, providing insights into factors that may interfere with more rapid sleep onset. The Sleep Hygiene Practice Scale (SHPS) [91] measures actions that help or hinder healthy sleep rhythms and routines. Finally, the Pittsburgh Sleep Quality Index (PSQI) [92] measures global sleep quality across several domains, including daytime dysfunction, sleep duration, disturbances, and sleep onset latency. Together, these self-reports offer a multidimensional assessment of sleep-focused processes that may interact with or predict treatment response (Table 1 and Appendix B).

### Treatment-specific assessments

The following measures will be administered only to participants who are assigned to the Digital PAI arm.

#### Cultural relevance

Administered post-treatment, the Cultural Relevance Questionnaire (CRQ) [93] is a self-report assessment that measures the cultural relevance of the Digital PAI modules or sessions to the specific cultural context in Singapore, particularly in Southeast Asia. Cultural relevance is measured along three dimensions. Functional equivalence is the degree to which the participant perceives that the Digital PAI characterizes their mental health challenges well and interprets them in culturally sensitive ways. Conceptual equivalence is the extent to which the Digital PAI assesses the same mental health concepts in the participant’s culture. Linguistic equivalence is the degree to which the language and jargon used in the Digital PAI were culturally sensitive. Participants will rate the extent of functional, conceptual, and linguistic equivalence on a 5-point Likert scale (1 = *components are not reflected well within the module* to 5 = *all of the components are reflected within the module*) for each Digital PAI session.

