### Sample size and power

The *R* package *simr* [56] was used for power calculations, which simulated a multilevel model with time and group as fixed effects. The primary outcomes are anxiety and depressive symptoms, indexed by GAD-7 and PHQ-9 scores, respectively. Given the low-intensity nature of the Digital PAI and its evaluation against a Self-Monitoring Placebo as a placebo control [57], we expected the between-treatment effect sizes to range from small (Cohen’s *d* = 0.2) [26, 58] to moderate (*d* = 0.5) [24]. To achieve a statistical power of 81% while detecting small to moderate between-group efficacy effect sizes at a 5% significance level, a sample size of between 300 and 1,600 is required. Accounting for an estimated 50% attrition rate, our planned sample size was 1,200 (600 participants per group).

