#### Perceived helpfulness

Administered at the end of each 30-minute Digital PAI session, participants will be asked to complete the Helpful and Hindering Aspects of Therapy (HAT) Questionnaire [94–96]. The HAT Questionnaire captures what the participant experienced as most and least helpful during the session, as well as their main takeaways. It also asks participants if any part of the Digital PAI content during the session might have been hindering.

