#### Treatment satisfaction

Administered post-treatment, the Satisfaction with Treatment Questionnaire (STQ) [97] is a self-report assessment of participants’ satisfaction with the guidance provided in the on-demand Digital PAI content. The STQ also captures the degree of helpfulness, user-friendliness, and subjective effectiveness of the Digital PAI content. Participants will rate on a 5-point Likert scale (0 = *disagree very strongly* to 4 = *agree very strongly*). Two open-ended questions will also be asked at the end of the STQ, allowing participants to share what they liked and disliked about the Digital PAI, thereby providing an opportunity for them to share their qualitative experiences.

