### Weekly digital PAI 30-minute sessions during the 6-week intervention phase

Table 2 provides an overview of the Digital PAI content. PAT was initially developed by [name] and colleagues at the University of California, Los Angeles, to address difficulties in reward processing, specifically problems with wanting, liking, and learning about positive experiences [98]. The lead author ([name]) locally tailored this intervention for digital delivery and culturally tailored it for adults living in Singapore. Thus, the 6-week Digital PAI was adapted from the 15-week face-to-face, therapist-led PAT manual [98]. Digital PAI comprises 8 sequential online 30-minute sessions, each starting with a brief pre-recorded video to orient the user, and is provided over 6 weeks, each addressing key exercises linked to fostering PA and reducing anhedonia. The first few sessions teach participants about the characteristics of dampened positive emotions (Session 1) and offer psychoeducation on the aims, rationale, and structure of the Digital PAI, highlighting its scientifically informed approach (Sessions 2 and 3). In the following sessions, participants learn the skills to detect and change maladaptive patterns connecting actions, behaviors, and cognitions (Session 4). Session 5 equips participants with skill-building practices that foster engagement in independent and social activities that are experienced as congruent with one’s values, pleasurable, and rewarding, thereby enhancing everyday positive reinforcement. The Digital PAI further coaches participants to purposefully attend to, amplify, and maintain focus on positive experiences via generosity, gratitude, and related positive psychology–informed exercises (Session 6). Participants also learn to proactively create and consolidate positive moods through techniques such as positive reappraisal, reward sensitivity exercises, and positive reframing (Session 7). Finally, participants are encouraged to strengthen and sustain their learning by creating individualized skills consolidation plans and preparing for the lifelong practice of these skills in their daily routines beyond the formal Digital PAI program (Session 8). Between all sessions, EMIs will be provided to Digital PAI participants to help them apply their skills in multiple daily, real-world settings. Moreover, the Digital PAI offers guidance-on-demand, such that users can contact a trained study team member who will offer asynchronous coaching on users’ queries about applying skills learned in the program and related therapeutic processes.

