### Statistical analysis plan

#### Data processing and missing data management

All preprocessing steps and data analyses will be conducted using the *R* software [113]. Using an intention-to-treat (ITT) approach, we will estimate between-group treatment efficacy for continuous and binary clinical outcomes [114]. A complier average causal effects (CACE) analysis will also be conducted to determine treatment efficacy between high- and low-potential engagers [115]. Before conducting the key data analyses, a series of preprocessing steps will be undertaken. These include anomaly diagnostics, assumption checks (e.g., linearity, multivariate normality), and random forest imputation of missing data. Random forest imputation with the *missRanger* package [116] will be used instead of multiple imputation because it better handles nonlinear associations and interactions and generates improved performance even under missing not-at-random (MNAR) conditions [117]. Sensitivity analyses will be conducted by examining outcomes under two alternative missing data management approaches, full information maximum likelihood (FIML) and multiple imputation [118]. The point estimates and 95% confidence intervals (CIs) of all effect sizes, Cohen’s *d* for continuous outcomes [119], as well as odds ratios [ORs] and risk ratios [RRs] for binary outcomes [120], will also be computed consistently.

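### The CRQ asks for ratings of every Digital PAI session but is given only once, at Week 6, so participants who have left by then rate none of the sessions they took

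*Protocol article*

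**What the plan says.** All references are to the Protocol article.

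- **Who receives it.** Under Treatment-specific assessments, the CRQ, HAT and STQ go to the intervention arm as assigned: "The following measures will be administered only to participants who are assigned to the Digital PAI arm". No session-completion condition is attached.
- **When.** Under Cultural relevance: "Administered post-treatment, the Cultural Relevance Questionnaire (CRQ". Table 1 agrees, with a single mark for the CRQ in the Week 6 column.
- **What is rated.** The same section asks for functional, conceptual and linguistic equivalence, each on a scale from 1 to 5, "for each Digital PAI session".
- **How many sessions.** The section on the weekly sessions states: "Digital PAI comprises 8 sequential online 30-minute sessions". Table 2 places Sessions 1 to 3 in Week 1. The Abstract gives six sessions instead.
- **The neighbouring measures.** The HAT is collected session by session: "Administered at the end of each 30-minute Digital PAI session, participants will be asked to complete the Helpful and Hindering Aspects of Therapy (HAT) Questionnaire". The STQ is collected once: "Administered post-treatment, the Satisfaction with Treatment Questionnaire (STQ".
- **Leaving.** Symptom assessments lets participants stop the intervention whenever they wish. Protocol adherence and engagement strategies separately lets them withdraw from the study, after which nothing further is required of them.

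**The concern.** The rating unit is the session, but the collection point is the end of the programme. A participant who takes Sessions 1 to 4 and then withdraws has formed a view of four sessions, and the schedule never asks for it. No analysis plan can recover ratings that were not collected, so this is a matter of the stated administration time and not a detail left to the SAP.

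The loss may be selective. Poor cultural fit is a plausible reason to leave, and the CRQ is the measure of cultural fit; the HAT and STQ ask about helpfulness and satisfaction. If leavers would have rated lower, the reported means are too favourable. The Discussion presents local tailoring as a strength and looks to use in other culturally diverse settings, so a favourable rating could later be cited in support. Recall is a second, smaller problem, and it is greatest for the three Week 1 sessions.

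**Working it through.** The plan gives no figure for this point to reproduce. The check sets the stated timings side by side and then works out a range under stated assumptions.

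**1. Burden and recall**

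- Ratings requested in the one sitting: 3 dimensions × 8 sessions = 24. With the Abstract's session count, 3 × 6 = 18.
- Recall interval for Week 1 sessions: Week 6 − Week 1 = about 5 weeks. The HAT for the same sessions is answered at the end of each.

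**2. Who can give a rating**

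| Path | CRQ under the stated schedule |
|---|---|
| Takes all sessions, answers at Week 6 | All sessions rated |
| Skips sessions or stops the intervention, answers at Week 6 | Sessions taken can be rated; nothing excludes this person |
| Withdraws from the study before Week 6 | No rating, including for sessions taken |
| Remains enrolled but does not answer at Week 6 | No rating, including for sessions taken |

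The population is therefore Week 6 respondents.

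**3. Possible size**

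Inputs:
- Intervention arm: 600 (Sample size and power).
- Loss by Week 6, L: not stated. The only dropout figure is "Accounting for an estimated 50% attrition rate, our planned sample size was 1,200", which has no time point, in a trial followed to 12 months. L is assumed to lie between 0% and 50%.
- Gap g, the respondents' mean rating minus the mean that those lost would have given: not stated. Assumed 0.25 to 1.0 point on the 5-point scale.

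Respondents = 600 × (1 − L). This gives 600 at 0% loss, 540 at 10%, 420 at 30% and 300 at 50%.

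If respondents have mean m and those lost have mean m − g, the mean over everyone is (1 − L)m + L(m − g) = m − Lg. The overstatement is therefore L × g.

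| L | g = 0.25 | g = 0.5 | g = 1.0 |
|---|---|---|---|
| 0% | 0 | 0 | 0 |
| 10% | 0.025 | 0.05 | 0.10 |
| 30% | 0.075 | 0.15 | 0.30 |
| 50% | 0.125 | 0.25 | 0.50 |

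For any one session, L should be read as the share of those who took it and gave no CRQ rating. It equals the loss from the whole arm only for a session that everyone took. For later sessions some leavers had already gone, so fewer of those who took the session are missing. If leavers would not have rated lower, g is zero or negative and there is no overstatement.

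**The case against.** The strongest reply is that nothing here is inconsistent. The text and Table 1 agree on one retrospective administration with session-by-session items, and that spares participants who already receive 126 prompts and a HAT after every session. Cultural fit is not an aim, a hypothesis or a listed primary or secondary outcome. Engagement logs and the HAT, which asks about hindering content, already capture part of what early leavers experienced. Rating at the end of each session would not remove selection either, since later sessions would still be rated only by those who reach them. All of this stands. It limits the importance of the point, but it does not restore the ratings of people who took sessions and then left.

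Three stronger readings are tempting, and the documents do not support them.

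- **That only participants who completed every session are described, and others cannot be scored.** The CRQ goes to the arm as assigned. Stopping the intervention is described separately from withdrawing from the study, and only withdrawal is said to end procedures.
- **That ratings of unopened sessions will be imputed.** The missing-data paragraph lists "and random forest imputation of missing data" among the steps before the key analyses, in a paragraph about between-group efficacy on clinical outcomes, and names two alternative approaches as sensitivity analyses. It does not mention the CRQ, which exists in one arm only. Scoring rules for sessions not taken may sit in the full protocol or SAP.
- **That half the arm will be missing at Week 6, or that ratings will certainly be inflated.** The 50% carries no time point, and the direction of any bias is an assumption.

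**Conclusion.** The point holds as a modest limitation of the design. Per-session ratings taken once at Week 6 leave out the views of participants who have left the study by then, including on sessions they took, and rely on about five weeks' recall for the Week 1 sessions. The results should be described as those of Week 6 respondents.

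The overstatement lies between 0 and 0.50 point on the 5-point scale. That range rests on an assumed Week 6 loss of 0% to 50%, an assumed gap of 0.25 to 1.0 point, and leavers rating lower. The documents establish none of the three. The consequence stays within a descriptive acceptability measure and does not reach the GAD-7 or PHQ-9 comparison. This is a cheap improvement and not a condition for the trial's validity.

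**What to change.** Collect the three CRQ ratings for a session at the end of that session, alongside the HAT, and amend the Cultural relevance section and the CRQ row of Table 1 to match. Report the ratings per session, with the number who opened the session and the number who rated it. The STQ can stay at Week 6 as an overall judgement, described as coming from Week 6 respondents.

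Costs:
- Three more items after each session, offset by removing up to 24 at Week 6. A participant who takes all eight sessions answers no more items in total.
- Selection and recall error are reduced but not removed. Later sessions are still rated only by those who stay, and someone who opens a session without finishing it may give no rating.
- Recruitment is under way, so participants already enrolled under the Week 6 schedule must be reported separately from those who rate at each session.

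If the sponsor prefers not to change the schedule during recruitment, the minimum is to label the CRQ results as those of Week 6 respondents and to give the number rating each session beside the number who opened it.

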#### Perceived helpfulness

Administered at the end of each 30-minute Digital PAI session, participants will be asked to complete the Helpful and Hindering Aspects of Therapy (HAT) Questionnaire [94–96]. The HAT Questionnaire captures what the participant experienced as most and least helpful during the session, as well as their main takeaways. It also asks participants if any part of the Digital PAI content during the session might have been hindering.

#### Treatment satisfaction

Administered post-treatment, the Satisfaction with Treatment Questionnaire (STQ) [97] is a self-report assessment of participants’ satisfaction with the guidance provided in the on-demand Digital PAI content. The STQ also captures the degree of helpfulness, user-friendliness, and subjective effectiveness of the Digital PAI content. Participants will rate on a 5-point Likert scale (0 = *disagree very strongly* to 4 = *agree very strongly*). Two open-ended questions will also be asked at the end of the STQ, allowing participants to share what they liked and disliked about the Digital PAI, thereby providing an opportunity for them to share their qualitative experiences.

### Weekly digital PAI 30-minute sessions during the 6-week intervention phase

Table 2 provides an overview of the Digital PAI content. PAT was initially developed by [name] and colleagues at the University of California, Los Angeles, to address difficulties in reward processing, specifically problems with wanting, liking, and learning about positive experiences [98]. The lead author ([name]) locally tailored this intervention for digital delivery and culturally tailored it for adults living in Singapore. Thus, the 6-week Digital PAI was adapted from the 15-week face-to-face, therapist-led PAT manual [98]. Digital PAI comprises 8 sequential online 30-minute sessions, each starting with a brief pre-recorded video to orient the user, and is provided over 6 weeks, each addressing key exercises linked to fostering PA and reducing anhedonia. The first few sessions teach participants about the characteristics of dampened positive emotions (Session 1) and offer psychoeducation on the aims, rationale, and structure of the Digital PAI, highlighting its scientifically informed approach (Sessions 2 and 3). In the following sessions, participants learn the skills to detect and change maladaptive patterns connecting actions, behaviors, and cognitions (Session 4). Session 5 equips participants with skill-building practices that foster engagement in independent and social activities that are experienced as congruent with one’s values, pleasurable, and rewarding, thereby enhancing everyday positive reinforcement. The Digital PAI further coaches participants to purposefully attend to, amplify, and maintain focus on positive experiences via generosity, gratitude, and related positive psychology–informed exercises (Session 6). Participants also learn to proactively create and consolidate positive moods through techniques such as positive reappraisal, reward sensitivity exercises, and positive reframing (Session 7). Finally, participants are encouraged to strengthen and sustain their learning by creating individualized skills consolidation plans and preparing for the lifelong practice of these skills in their daily routines beyond the formal Digital PAI program (Session 8). Between all sessions, EMIs will be provided to Digital PAI participants to help them apply their skills in multiple daily, real-world settings. Moreover, the Digital PAI offers guidance-on-demand, such that users can contact a trained study team member who will offer asynchronous coaching on users’ queries about applying skills learned in the program and related therapeutic processes.

**Table 2 Tab2:** Summary of digital positive affect intervention (PAI) content

Week	Session	Session Title	Key Content and Intervention Strategies
Week 1	Session 1	Is it difficult for you to feel positive emotions?	Psychoeducation on anhedonia, the positive affect system (wanting, liking, learning), and the consequences of low positive affect; introduces case examples to contextualize symptom profiles.
	Session 2	How will this online intervention work for you?	Orientation to intervention structure, intervention fit and readiness assessments, rationale for targeting positive affect, and overview of modules.
	Session 3	Let’s get started	Guidance on using practice sheets, daily skill rehearsal, self-monitoring, and intervention pacing; introduces symptom tracking and exercise compliance strategies.
Week 2	Session 4	The triad of feelings, thoughts, and actions	Introduces the mood cycle model; teaches the interplay between cognitions, behaviors, and physical sensations in shaping mood; begins emotion labeling and upward spiral training.
Week 3	Session 5	Actions toward feeling better	Behavioral activation module focusing on identifying, scheduling, and practicing rewarding activities; includes activity monitoring, mastery-building, savoring, and troubleshooting motivational barriers.
Week 4	Session 6	Attending to the positive	Cognitive strategies to enhance attentional focus on positive experiences: finding silver linings, taking ownership of successes, and imagining positive outcomes to strengthen reward anticipation.
Week 5	Session 7	Building positivity	Positive affect cultivation through loving-kindness, gratitude, generosity, and appreciative joy exercises; emphasizes relational and compassion-based positive emotion generation.
Week 6	Session 8	Contributing to the journey after the intervention	Consolidation of gains, maintenance planning, relapse prevention, progress assessment, and preparation for long-term self-guided practice.

### Localization of the digital PAI

The PAT client manual [98] informed the development of the Digital PAI in Singapore through surface-level contextual and structural adjustments to better fit the local context. We locally tailored the Digital PAI to fit a 6-week, 30-minute-per-week structure in Singapore instead of the original 15-week, 45-minute-per-session format to fit local adults’ engagement patterns, time limitations, and digital access preferences while retaining the primary therapy elements. Contextual changes included modifying examples, names, and scenarios to reflect familiar settings and conventions. For instance, characters such as “Felix” and “Joy” were replaced with more locally recognizable names like “Wei Jie.” References to crisis and emergency support services were updated to include local resources such as the Singapore emergency hotline ([name]) and the 24-hour Samaritans of Singapore (SOS) hotline ([name]). Language was simplified to enhance clarity and relatability, with fewer Western idioms and greater use of locally meaningful examples, such as common work-related stressors. These contextual changes help ground the material in local social norms and values, including the emphasis on family harmony and productivity, while preserving the core principles of PAT.

Structural modifications included distilling the original PAT client manual into modular, thematically focused online sessions incorporating interactive elements and targeted exercises designed for mobile and web-based platforms. Between-session action plans were brief and flexible, allowing users to engage at their own pace. Each session was kept concise to accommodate the time constraints and learning preferences of busy Singaporean adults. Practices such as acts of generosity and savoring were adapted for digital use, with clear guidance on when and how to apply each technique. Despite these delivery adjustments, the foundational therapeutic progression, covering psychoeducation, behavioral activation, and strategies to build reward sensitivity and PA, remained intact.

